##### **B. Description of Population to be Enrolled:**

The populations to be enrolled will live in the United States, including urban and rural regions. Human subjects participation will include both patients and practice staff and clinicians.

- Participating patients age 16 and older identified by their clinician at a participating primary care practice as having opioid dependence or OUD and agreed to receive MAT. Participants will be patients of diverse types of practices, including Federally Qualified Health Centers, Rural Health Clinics, private practices, community health centers, and hospital-based practices.

Exclusion criteria: Patients will be excluded if they are hypersensitive to buprenorphine or naloxone, known to have serum aspartate aminotransferase or alanine aminotransferase levels greater than five times normal, and/or diagnosed with severe, untreated psychiatric illness. Patients with an existing preference for office-based or home MAT induction will not be eligible. If a patient is deemed ineligible for study participation or does not wish to participate, induction for MAT will occur using the practice's usual clinical protocol.

- Clinicians and staff at participating primary care practices. Primary care practices with at least one waived prescriber currently treating patients with OUD with buprenorphine will be invited to participate.

### **C. Study Design and Research Methods**

The study is a randomized, parallel group, two-arm pragmatic comparative effectiveness trial of two standard care models for induction (home or office-based) for MAT in primary care practices. Randomization will be at the patient level. We have designed our study to measure outcomes based on the primary comparators and important factors that may influence both the short-term and long-term success of MAT.

#### Community and Patient Engagement

This proposal is the direct result of questions and comments regarding office-based versus home inductions for MAT from practices, patients, community members, stakeholders, and practice facilitators around the country involved with the IT MATTTTRs™ Program. Local community and patient advisory councils from the HPRN and CaReNet contributed to the development of this study and are dedicated to ongoing collaboration in all aspects of the study. We will draw from our existing patients and community councils to form a Project Community Advisory Council, adding a small number of new members to round out the types of expertise and experiences present. We will hold meetings and regularly communicate with the Council between meetings to maintain progress and general communication. Specific activities will include the development of practice and patient recruitment materials, reviewing and assisting in the selection of survey instruments and study protocols, interpreting results, preparing and giving presentations at local and national meetings, and identifying and participating in other dissemination activities. Community members have and will participate in the Human Subjects Training for Community Members (submitted to COMIRB 7/7/2020, resulting from meeting with [name]; [name]; [name] (CCTSI); [name]; and [name], MSPH; 7/15/2014).

#### Recruitment

##### *Practice Recruitment*

Primary care practices with at least one waived prescriber currently treating patients with OUD with buprenorphine will be invited to participate. The study goal is to recruit 100 practices nationwide. In Colorado, we will recruit practices from the State Networks of Colorado Ambulatory Practices and Partners (SNOCAP) and will partner with other organizations that work with primary care practices to notify practices of the study. Based in the Department of Family Medicine, SNOCAP is the overarching name for the collaborative affiliation of practice-based research networks in Colorado that joined together to improve communication, facilitate joint research projects, and share research staff and resources. The SNOCAP PBRNs assisting with this study work closely with diverse primary care practices in urban and rural regions across the state.

Nationally, the Academy of Family Physicians (AAFP) National Research Network will recruit practices. The AAFP is the national professional association of family physicians. The AAFP NRN has conducted more than 80 studies and has over 2,300 clinician members in 1,000 diverse practices covering all 50 states, the District of Columbia, and Puerto Rico.

Practices will be notified of the study via recruitment flyer. The flyer will be sent to practices via emails and shared at in-person visits. The practice recruitment flyer will be submitted to COMIRB for approval prior to use.

### *Participant Recruitment*

- Patients

This study will enroll patients that the primary care provider believes would benefit from MAT with buprenorphine. As this study will occur with the patient's health care medical provider, the recruitment for participation in this study will occur in accordance with guideline-concordant screening, as part of usual care, by the practice care team to identify patients with OUD and patients with chronic pain that have opioid dependence and could benefit from MAT with buprenorphine. Primarily these are patients with opioid dependence and either 1) addiction as defined by DSM-V criteria for OUD and/or 2) chronic pain with long-term, high dose opioid use (greater than one year and morphine equivalent daily dose higher than recommended by the CDC). Participating practices will describe the options for induction (office or home) to patients who are opting to receive MAT, which is part of their usual care. Patients who are willing to use either type and meet criteria will be informed of the study verbally and given a study information sheet. If the patient is interested and willing to learn more about the study at that visit, referred here to as Time 1, the practice will call the central study team staff, who will describe the study in detail to the patient, including that participation involves randomization to office-based or home induction. If the patient is interested in participating, the study team staff will confirm eligibility, consent the patient, randomize the patient to the *office-based induction* arm or the *home induction* arm, and contact the practice with the study arm.

This study aims to enroll 1200 participants to reach a goal of 1000 retained participants receiving MAT (allowing for attrition prior to MAT induction). In Colorado, enrollment goals are 660 to retain 550 receiving MAT. We anticipate an average of 10 patients per practice will be screened for OUD or identified as opioid dependent, accept MAT induction, enroll in the study (accepting randomizing into home or office-based induction), and have monitoring data entered into the Practice Participant Tracker.

- Practice Clinicians and Staff

Participating clinicians and staff will be invited to participate in key informant interviews (approximately 2-3 people per practice) and surveys (all practice members). Participants will be identified from practice rosters maintained by the partnering PBRNs and with assistance from practice managers to confirm the number of practice staff.

## **Research Methods**

### Conceptual Framework

The project evaluation will be informed by the conceptual framework for this study, which is based on the Rubicon model of action phases (Achtziger & Gollwitzer) and self-determination theory (Ryan & Deci). The Rubicon model is a model of behavior change that addresses motivation to change and turning motivation into action. Phase 1 focuses on motivation (deciding to change and setting goals). Phase 2 focuses on planning (determining how, where, when and for how long a goal will be pursued,). In Phase 3, the focus is action

control (exerting effort to execute the plan). Phase 4 focuses on evaluation (consideration of the value of continued goal pursuit).

### Randomization

Patients who meet eligibility criteria and consent to participate will be randomized to either the *office-based induction* arm or the *home induction* arm. Both induction methods are evidence-based approaches for initiating MAT in patients with OUD. Participating practices will receive a suggested protocol for both office-based and home inductions. However, practices and providers experienced in MAT may have their own existing protocols for office and home induction. Given the pragmatic nature of this trial, we will allow some variation in induction protocols.

Randomization will occur at the patient level. Patients will be informed that participation includes randomization by the initial information handout they receive from the practice and again by the research team member during the consent process. Randomization will occur immediately following consent. A study coordinator will inform the participant of their randomization assignment. As consent will be completed by phone with the patient, the study team member will inform the participant of the study arm assignment (randomization result) while on the phone with the participant and then immediately inform the practice of the patient's assigned induction type.

A block randomization process will be used where patient participant "slots" will be randomized for each practice in advance of recruitment to ensure equal distribution between arms at each practice. This will increase our power to detect differences between study arms, as opposed to a cluster randomized trial. Further, this use of block randomization will provide the best opportunity for each practice to enroll patients in either arm of the study and for regular monitoring of enrollment across arms. Few previous studies on home and office-based MAT induction have been randomized trials. The study findings will be the result of rigorous research design and methods.

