##### *Randomization to Condition*

Patients will be randomized to either the office-based MAT induction arm or the home MAT induction arm. An average of 10 patients per practice will be enrolled, with an allowable range of 6 – 20 patients. Block randomization will be used to ensure an equal number of patients in each arm. The “slots” will be randomized for each practice in advance of recruitment to ensure equal distribution between arms at each practice. The result will be approximately 500 patients per study arm. For some outcomes (e.g., quality of life), we allow for ~20% attrition (leaving 800 patients total, 400 per arm).

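### Forcing equal arms within each small open-label practice makes the next assignment predictable to the people who decide, on a subjective preference screen, which patients are referred

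*Protocol*

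**What the plan says.** Three parts of the protocol bear on this.

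- **Balance inside each practice.** Under IV.C, Randomization, patient slots "will be randomized for each practice in advance of recruitment to ensure equal distribution between arms at each practice". Section IV.F, Randomization to Condition, repeats the aim: "Block randomization will be used to ensure an equal number of patients in each arm". It also gives the size of the unit: "An average of 10 patients per practice will be enrolled, with an allowable range of 6 – 20 patients". Neither section states a block size or says whether it varies.
- **Open arms, told at once.** After consent by telephone, the study team member gives the patient the result and must "then immediately inform the practice of the patient's assigned induction type". The Practice Tracker kept at the practice also records each participant's induction type.
- **The practice is the first gate.** Under Participant Recruitment, "Participating practices will describe the options for induction (office or home) to patients who are opting to receive MAT". Then: "Patients who are willing to use either type and meet criteria will be informed of the study verbally and given a study information sheet". Section IV.B adds: "Patients with an existing preference for office-based or home MAT induction will not be eligible". No objective definition of a preference is given. Only after referral does the central team act: "the study team staff will confirm eligibility, consent the patient, randomize the patient".

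**The concern.** Randomization protects the comparison only if whoever decides on entry cannot foresee the next arm. Here the practice holds the running count, knows that the arms are meant to come out equal, and applies a criterion that depends partly on how it describes the two methods. It also makes the referral call, or sends contact details later, so it influences the order of entry as well.

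The protocol's own background supplies ordinary, well-meant reasons to act on a guess. Section III says that office induction takes much staff time, that some practices are reluctant to commit it, and that some patients lack the social support or executive function that successful induction often needs. A clinician might hesitate to refer such a patient when a home slot looks due. If that happens often enough, the arms differ at entry on traits expected to bear on retention. Intention to treat keeps the arms as they were formed, so it carries the difference into the result.

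**Working it through.** **The plan's own figure.** The protocol gives no figure for predictability. Its sample-size figure serves as a yardstick, and it reproduces. For 500 per arm, 45% against 54%, two-sided 0.05: the null standard error is √(2 × 0.495 × 0.505 / 500) = 0.03162, the alternative standard error is √((0.45 × 0.55 + 0.54 × 0.46) / 500) = 0.03149, and (0.09 − 1.96 × 0.03162) / 0.03149 = 0.89. Power is 81.3%, against 81% stated. The trial is thus built to detect 9 points.

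**Predictability of the next arm.** Input from the protocol: equal allocation within practice, all past assignments known, about 10 patients per practice. Assumed: the block size. The guess is the arm with fewer assignments so far; ties count as one half.

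For a filled block of 2m:

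- Expected correct guesses = m + (4^m / C(2m, m) − 1) / 2.
- Expected assignments fully determined by those before them = 2m / (m + 1).

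For a block of 10 (m = 5): 5 + (1024/252 − 1)/2 = 6.53 of 10, or 65.3%; determined, 10/6 = 1.67 of 10.

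| List at the practice | Enrolled | Correct guesses | Determined assignments |
|---|---|---|---|
| Filled blocks of 2 | all | 75.0% | 1.00 per block |
| Filled blocks of 4 | all | 70.8% | 1.33 per block |
| One filled block of 10 | 10 | 65.3% | 1.67 |
| One filled block of 20 | 20 | 61.7% | 1.82 |
| One block of 12, not filled | 10 | 59.9% | 0.26 |
| One block of 20, not filled | 10 | 54.7% | 0 |
| One block of 10, not filled | 6 | 57.4% | 0.008 |

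A coin toss gives 50%. The last three rows come from exact recursion over the slots that remain. The guess needs only the running count at the practice. Certainty also needs the block size to be known or inferred.

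**Does varying the block size cure it?** Simulated lists of 10 patients (40,000 per setting), with sizes drawn at random within practice and the same guess: sizes 2 and 4, 71%; sizes 2, 4, 6 and 8, 67%; sizes 4, 6 and 8, 66%. Small varied blocks take away near-certainty but guess no worse than one block of 10. What lowers the guess rate is a block that is large relative to the practice.

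**What steering could do.** This is illustration, not forecast. Assume 100 practices of 10, no true arm effect, two equally common prognosis groups with success 64.5% and 34.5%, and a patient who does not fit the predicted arm is held back with probability q (200 runs, so the rates are rough).

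| q | Blocks of 2 | Blocks of 4 | Blocks of 10 |
|---|---|---|---|
| 0.25: spurious difference (false-positive rate) | 2.3 points (11%) | 1.7 (6%) | 1.2 (6%) |
| 0.50: spurious difference (false-positive rate) | 4.8 points (35%) | 3.7 (21%) | 3.3 (16%) |

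With q = 0 there is no bias.

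**The case against.** The strongest reply is that much of this may already be handled. Block sizes are commonly kept out of a protocol that sites can read, and a separate randomization plan may hold varied, concealed blocks. That stands, so the missing block size is not the fault. The stated aim of equality within units of 6 to 20 patients is, because it creates predictability under every block size tried.

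Second, the central team confirms eligibility and obtains consent before randomizing. This also stands, and it protects against direct use of the list. It cannot recover patients who were never referred.

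Third, baseline executive function and substance use are measured, and the Quantitative Analytic Plan compares the arms at baseline and adjusts for covariates related to outcome. That is a partial safeguard; a clinician's unrecorded judgement stays outside it. Practices are also paid for each patient enrolled, which works against holding patients back.

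Three stronger readings are tempting, and the documents do not support them:

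- A reader might infer that 170 to 200 assignments are certain in advance. That needs every practice to have exactly one block of 10, know it and fill it. With 12 slots and 10 enrolled, only 0.26 per practice are determined.
- A reader might see a contradiction between the preference exclusion in IV.B and the willingness screen in Participant Recruitment. The latter also requires the patient to meet the criteria, which brings in the exclusion, so the two conditions add up.
- A reader might infer that central staff see the list while judging eligibility. The text does not say so, and it places eligibility and consent before randomization.

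**Conclusion.** The concern holds as a design weakness: equal allocation within small open-label practices, immediate disclosure of each arm and a subjective referral screen in the same hands together let a practice predict the next arm better than chance and act on it. Depending on the assumed block size and on how far the list is filled, the best guess is right in about 55% to 75% of cases; one filled block of 10 gives 65%. Certainty about individual assignments ranges from none to a sizeable share and requires knowledge of the block size. No bias is demonstrated. Its size rests on practice behaviour that the documents do not give: in the illustration it runs from zero to almost 5 points, against the 9 points the trial is powered to detect. The sample-size figures are unaffected. The change should be made because it is cheap and the exposure cannot be repaired afterwards.

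**What to change.** In IV.C, Randomization, and IV.F, Randomization to Condition, replace the aim of equal arms at each practice with approximate balance. State that a central concealed list is used, that block sizes vary at random, and that they are withheld from practices and from the staff who screen and consent. Make blocks large relative to the practice, or stratify on a unit larger than the single practice. Keep the actual sizes in a restricted document.

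The cost is a regenerated list and some imbalance within practices. In a practice of 10, a split of 7 to 3 or worse has probability 2 × (1 + 10 + 45 + 120)/1024 = 34% if assignments there behave like coin tosses, and 2 × (1 + 100 + 2025 + 14400)/184756 = 18% for a half-filled block of 20. The practice random effect already planned in the Quantitative Analytic Plan accommodates this, so exact balance at each practice is not needed for the analysis.

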### *Office-based and Home Induction Protocols*

Standard observed, office-based induction includes the practice staff or clinician assessing the patient for level of withdrawal, administering the first dose of medication, monitoring the patient, and administering subsequent doses of medication at the practice. Patients are given a follow-up plan, including a dosing schedule for the next day, indications of when to call the practice, a follow-up contact schedule (calls or in-person appointment the next day), and an appointment for later in the week.

Standard unobserved, home induction includes giving patients instructions on induction steps. Participants doing home inductions self-assess and determine when they are in adequate withdrawal to administer their first dose of buprenorphine. With home induction, patients administer their initial dose of buprenorphine, assess withdrawal symptoms using the SOWS, and administer subsequent doses of buprenorphine themselves. If practice is aware of when home induction will occur, a member of the practice team might contact patient to assess progress as needed. Patients follow up as agreed upon with their practice team.

### Consent

Subjects recruited for this study include practice staff and patients. This project poses minimal risk to study participants. Participation is voluntary. Patient participants may be

uncomfortable answering questions about buprenorphine prescription or illicit opioid use and other aspects of their lives. Participants can refuse to answer any questions they want. Key informant interview participants can determine the information they share during their interviews. Consent will be obtained.

### *Patients*

Interested potential participants (with a diagnosis of OUD and seeking to begin MAT) will receive a study informational packet at their clinic, which will include a copy of the [Postcard Consent Form](#). The practice will call the research team member assigned to them with the patient's contact information for patients that have expressed interest in the study and given the practice permission to initiate contact with the research team. If the patient is interested and willing to learn more at that visit, referred here to as Time 1, the practice will call the research team member assigned to them with the patient's contact information for patients that have expressed interest in the study and given the practice permission to initiate contact with the research team. A member of the research team will describe the study in detail to the patient, confirm eligibility, consent and randomize the patient, and contact the practice with the study arm. If this step cannot occur at Time 1, the practice will transmit to the central study team the interested and eligible patients' contact information for later informed consent and randomization. The goal will be to contact eligible, interested patients within 4 days of Time 1. At what is referred to here as Time 2, the patient will undergo MAT induction, per protocol for the method (home or office-based). We will strive to complete consent and randomization such that practices schedule Time 2 (induction) with 5 – 15 days of Time 1.

A signed, hard copy of the [Postcard Consent Form](#) will not be required from participants. The research team member will obtain and document verbal consent in REDCap. The [Postcard Consent Form](#) will explain that participation is voluntary and that they can discontinue participation at any time, the nature of participation, and that all data are confidential. For children age 16 and 17, we will obtain parent or guardian contact information to contact the parent. Parents or guardians will be informed of the study purposes and procedures. We will contact the child to obtain assent only after consent is obtained from the parent or guardian.

Although patients will be consented, each survey will still include a brief Information Sheet reviewing the conditions of participation, including that participation is voluntary and confidentiality. In addition to documentation of verbal consent by the study team, completion of surveys and assessments will imply consent.

### *Practice Clinicians and Staff*

Practice team members' survey will include an Information Sheet. Completion of surveys and interviews will imply consent.

For practice team members participating in key informant interviews, the research team interviewers will review the content of an Information Sheet with interview participants. All efforts will be made to provide an environment where questions are welcome and where questions can be answered privately, if preferred by the participant.

All members of the project team are trained in human subjects research and HIPAA.

